### Planned trial interventions

Surgical clipping or endovascular coiling is performed once for each patient. In the setting of multiple aneurysms, more than one aneurysm can be treated in the same sitting. Treatment will be initiated as soon as possible given local logistical constraints, according to standard of care of patients with ruptured aneurysms. Aneurysms thought by the treating teams to require deliberate permanent parent vessel occlusion, construction of a surgical bypass, or other flow-redirecting treatments that do not directly clip the aneurysm will not be excluded; these non-ISAT aneurysms are expected to be more difficult to manage with either surgical or endovascular methods.

### Inclusion/exclusion criteria

#### Inclusion criteria

Patients at least 18 years of age; at least one documented, intradural, intracranial aneurysm, ruptured within last 30 days; SAH World Federation of Neurological Surgeons (WFNS) grade 4 or less; the patient and aneurysm are considered appropriate for either surgical or endovascular treatment by the treating team.

#### Exclusion criteria

Patients with absolute contraindications of administration of contrast material (any type); patients with arteriovenous malformation-associated aneurysms; aneurysm located at basilar apex.

ISAT II will be a pragmatic trial; inclusion criteria will be kept loose and exclusion criteria minimal. The intent of ISAT II is not to repeat the initial ISAT. We expect ISAT II patients to be those for whom patient or aneurysm-related characteristics would not have led to their inclusion in ISAT, but for whom endovascular treatment is now contemplated. In other words, we are aiming to enroll patients to whom the global results of ISAT may not directly apply. As a general rule, patients previously referred to clipping despite the results of ISAT should now be considered for ISAT II. Similarly, patients considered for coiling, but with the assistance of devices that were not used in the original ISAT trial, such as stents, should be considered for ISAT II.

One exception in our pragmatic policy of as few exclusion criteria as possible is that we have chosen to exclude basilar apex aneurysms from the ISAT II study. Especially in the current climate, where surgical expertise with ruptured aneurysms in this notoriously challenging location is disappearing, this means the majority of ruptured aneurysms in this location will be treated with endovascular methods.

### Method of allocation

After confirmation of inclusion and exclusion criteria, patients will be randomly allocated 1:1 to either surgical or endovascular management, using a centralized minimization procedure. The following factors will be balanced between groups: i) age ≥70; ii) WFNS grade >3; iii) aneurysm size ≥10 mm (using maximum aneurysm diameter on cross-sectional imaging, with the outer diameter used for partially thrombosed aneurysms); and iv) posterior circulation location. The entire randomization procedure will be performed using a web-based platform available 24 hours a day.

### Justification of minimization criteria

#### Patient age

Subgroup analyses from ISAT point to a potential benefit from surgery in patients older than 70, who overall do worse than younger patients, whether they are treated one way or another. To ensure that this risk factor remains balanced between treatment groups, we have included age ≥70 (date of randomization on or beyond 70^th^ birthdate) as a minimization criterion.

#### SAH grade

Patients with Grade V aneurysm rupture, with a high mortality rate, will be excluded. Initial SAH grade is predictive of outcome [18-21]. Thus we will balance the number of poor (WFNS IV) grade SAH patients in each group.

#### Aneurysm size

Aneurysms 10 mm or larger may have greater treatment-associated risks, as well as a greater risk of incomplete occlusion and/or recurrence [18,22-25].

#### Aneurysm location: middle cerebral artery bifurcation and posterior circulation

Posterior circulation aneurysms have been associated with worse prognosis for both clipping and coiling [5]. For this reason, lesions in the different circulations will be minimized to ensure balanced groups, although we expect posterior circulation aneurysms will represent a minority of patients. Middle cerebral artery (MCA) aneurysms are common, but they were under-represented in ISAT. While they are increasingly treated with coiling, the best option remains unknown. We will monitor clinical results of treatments of MCA aneurysms separately, but this location will not be a minimization criterion.

### Anticipated use of adjunct devices

These devices are likely to be used in more difficult lesions; they necessitate the addition of a double antiplatelet regimen that may increase risks when aneurysms are treated in the early phase of SAH [26-28]. Results in this group will be monitored separately, but anticipated use of an adjunct device will not be a minimization criterion.

### Number of patients

With target alpha 0.05 and power 90%, a sample size of 1,724 patients (862 per group, no losses) would be sufficient to demonstrate a significant difference, using estimated 23% and 30% poor clinical outcome rates for endovascular treatment (EVT) and surgical management at one year, respectively (two-sided Fisher’s exact test). We expect very few losses to follow-up (<10%), and the target sample size is 1,896 patients.

### Planned patient follow-up

All patients will be seen in clinic at six to eight weeks, as part of routine follow-up care, followed by a telephone call at six months and another routine clinic visit at one year. These intervals will serve to determine mRS scores, and to inquire about possible aneurysm re-rupture. All patients will have non-invasive imaging (CTA or MRA) at six months to one year post-treatment to determine the presence of a major, saccular aneurysm recurrence. This follow-up is considered to be standard of care. There will be a study phone interview at five years to optimize long-term follow-up (Table 1).

**Table 1 T1:** Schedule of evaluations

**Evaluation**	**Screening**	**Pre-entry**	**Entry**	**Treatment**	**Discharge**	**6 months**	**1 year**	**5 years**
Documentation of RIA	X							
Imaging*	X						X	
Informed consent			X					
Medical history		X						
Clinical assessment		X			X		X	
Neurological exam		X			X		X	
Failure to occlude aneurysm				X				
Number of days in hospital					X			
Discharge disposition					X			
Major (saccular) aneurysm recurrence							X	
Hemorrhage during FU						X	X	X
Telephone interview						X		X

*Including catheter angiography or non-invasive imaging.

### Planned analyses

The main statistical tests will involve comparisons between the probability of reaching the primary end-point (dependent survival or death at one year) with a surgical or endovascular management strategy. Descriptive statistics will be done on demographic variables and potential risk factors to compare the two groups at baseline. Means, standard deviations, and ranges will be presented for quantitative variables such as size of aneurysms and frequency tables for categorical variables (such as the number of patients with multiple aneurysms). Statistics will be broken down by center and by treatment arm. Comparison of the groups will be assessed through independent ANOVA (quantitative data) or Mantel-Haentzel and *χ*^2^ tests (categorical data). Assuming comparability of groups across centers, the primary outcome will be compared between groups using a Fisher’s exact test at one year.

Secondary outcomes will be compared using independent *t*-tests for quantitative variables and *χ*^2^ tests for categorical variables. The analyses of follow-up data will control for baseline data using logistic regression, ANCOVA or Cox regression multivariate methods. All tests will be interpreted with a 0.05 level of confidence.

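### The primary Fisher's exact test leaves out the four minimisation factors; it is valid and meets its stated power, but it is conservative, and an adjusted primary analysis would gain about 1 to 3 points of power at no cost.

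*Protocol article*

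**What the plan says.** Under Method of allocation, patients are assigned 1:1 by centralised minimisation. "The following factors will be balanced between groups" introduces four of them: age 70 or over, WFNS grade above 3, aneurysm size of 10 mm or more, and posterior circulation location. The justification sections give the reasons. Age is called a risk factor, on grade the text says "Initial SAH grade is predictive of outcome", large size is tied to treatment risk and incomplete occlusion, and posterior location to worse prognosis.

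Planned analyses first compares the arms at baseline with ANOVA, Mantel-Haenszel and chi-square tests. It then fixes the primary test: "Assuming comparability of groups across centers, the primary outcome will be compared between groups using a Fisher’s exact test at one year". No covariate or stratum enters it. The next paragraph, which opens with secondary outcomes, adds that follow-up data will be analysed with control for baseline by logistic regression, ANCOVA or Cox regression. It lists no covariates. Stratification of results says outcomes will be stratified by the minimisation criteria, next to a sentence on safety-board monitoring of subgroups.

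Number of patients uses the same test ("two-sided Fisher’s exact test"): "With target alpha 0.05 and power 90%, a sample size of 1,724 patients (862 per group, no losses) would be sufficient", "using estimated 23% and 30% poor clinical outcome rates for endovascular treatment (EVT) and surgical management at one year, respectively".

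**The concern.** Minimisation forces the arms to be alike on factors that predict outcome. The difference in poor-outcome rates then varies less between hypothetical repetitions of the trial than an unadjusted 2x2 table assumes. A test that ignores the factors uses too large a variance, so its real type I error falls below 0.05. Fisher's test is already conservative because of the discreteness of the table. Both effects cost power in a trial that expects to recruit for about ten years, while the covariates that would recover it are recorded at randomisation.

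The opening clause of the primary-analysis sentence is a second, smaller matter. It ties the primary comparison to comparability of the groups and does not say what happens if comparability is doubted. In a randomised trial the primary analysis needs no such condition.

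**Working it through.** **Inputs from the article.** Rates 23% and 30%, two-sided alpha 0.05, power 90%, 862 per arm, Fisher's exact test, target 1,896 with losses below 10%.

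**Inputs that are assumptions.** The article gives neither the prevalence nor the strength of the factors. Assumed prevalences for age, grade, size and location are 15%, 20%, 25% and 10%. Assumed odds ratios are weak 1.5/1.5/1.3/1.3, moderate 2/3/1.5/1.5 and strong 3/5/2/2. The share of outcome variance explained by the factors (R²) is then 0.015, 0.068 and 0.145.

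**Step 1: reproduce 862.** Let p̄ = 0.265 and δ = 0.07.
- Uncorrected: n = [1.960·√(2·0.265·0.735) + 1.2816·√(0.23·0.77 + 0.30·0.70)]² / 0.07² = (1.2233 + 0.7974)² / 0.0049 = 833.3, so 834.
- Continuity-corrected (the usual approximation to Fisher): (833.3/4)·[1 + √(1 + 4/(833.3·0.07))]² = 861.6, so **862**. The article's figure is reproduced.
- The choice of test alone accounts for 862 − 834 = 28 per arm, or 56 patients.

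**Step 2: exact properties without covariates.** These come from full enumeration of the 2x2 tables.

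| Per arm | Fisher size (common rate 26.5%) | Fisher power | Chi-square size | Chi-square power |
|---|---|---|---|---|
| 862 | 4.40% | 90.06% | 5.01% | 91.0% |
| 853 (1,896 × 0.90 / 2) | 4.41% | 89.8% | 5.00% | 90.7% |

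**Step 3: add balance on the factors.** If the arms are balanced on the factors, the true standard deviation of the unadjusted difference is k = √(1 − R²) times what the 2x2 table assumes. A Fisher size of 4.40% corresponds to a critical z of 2.014. The standard errors are √(0.38955/862) = 0.02126 under the null and √(0.3871/862) = 0.02119 under the alternative. Then:
- Fisher size = 2Φ(−2.014/k)
- Fisher power = Φ[(0.07 − 2.014·0.02126)/(0.02119·k)]
- Adjusted power = Φ[(0.07 − 1.96·0.02126·k)/(0.02119·k)]

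| Factors | k | Fisher size | Fisher power | Adjusted power | Gain (points) |
|---|---|---|---|---|---|
| weak | 0.9925 | 4.2% | 90.2% | 91.3% | 1.2 |
| moderate | 0.9654 | 3.7% | 90.8% | 92.7% | 1.9 |
| strong | 0.9247 | 2.9% | 91.7% | 94.6% | 2.9 |

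**Step 4: simulation.** The set-up was 1,724 patients and minimisation with an assumed biased coin of 0.8, with 3,000 null and 1,500 alternative trials per scenario.

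| Factors | Type I error: Fisher | Type I error: adjusted | Power: Fisher | Power: adjusted |
|---|---|---|---|---|
| weak | 4.9% | 5.6% | 89.0% | 90.0% |
| moderate | 4.0% | 4.7% | 90.7% | 92.6% |
| strong | 3.6% | 5.4% | 92.1% | 94.4% |

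The 95% Monte Carlo error is about ±0.8 points for type I error (1.96·√(0.05·0.95/3,000)) and ±1.5 for each power (1.96·√(0.9·0.1/1,500)). The two methods agree broadly. The formula gives somewhat lower sizes because it assumes complete balance, which minimisation only approximates. With weak factors the simulation shows no clear conservatism beyond Fisher's own.

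**The case against.** The strongest reply is that design and analysis agree. The trial was sized for Fisher's test, uses Fisher's test and reaches its stated 90% power at 862 per arm. Its error is on the safe side, since a real type I error below 5% makes no false claim of benefit more likely. All of this stands. A reader might infer from the word conservative that the trial is underpowered or the test invalid, and the figures support neither. Even at the full 10% loss, exact power is 89.8%.

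A reader might also infer that the baseline tests decide which primary analysis is run, so that the analysis is chosen after the data are seen. The article does not say so. The clause speaks of comparability across centres and can be read as a premise rather than a gate. A figure such as 1 − 0.95¹⁰ = 40% for at least one false imbalance would need ten independent baseline variables and a rule that any one of them triggers a switch. The article states neither.

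It could further be said that adjustment is already planned. The sentence on control for baseline may well reach one-year mRS, but it names no covariates, offers three methods and does not replace the test named as primary. The stratification section sits with subgroup monitoring. Neither makes an adjusted model primary.

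Finally, the absence of a risk difference or confidence interval from this paragraph is no fault. An article commonly leaves that to the full protocol or analysis plan.

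**Conclusion.** The point holds as an efficiency recommendation. The primary test leaves out factors that the allocation balances and that the article itself links to prognosis or treatment risk. Fisher's size of 4.4% at 862 per arm is exact and needs no assumption about the factors, and about 0.9 points of power are lost through that alone (91.0% − 90.06%). The further figures, a size of roughly 3% to 4.5% and a total loss of about 1 to 3 points against an adjusted analysis, depend on assumed prevalences and odds ratios. They lie near the small end if the factors are weak. No stated operating characteristic fails at 862 per arm. The comparability clause is ambiguous wording that serves no purpose and is better removed; it does not show a data-driven analysis.

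**What to change.** In Planned analyses, replace the primary-analysis sentence with wording such as: *The primary analysis is a logistic regression of mRS >2 at one year on allocated arm and the four minimisation factors (age ≥70, WFNS grade >3, aneurysm size ≥10 mm, posterior circulation location), by intention to treat. It is reported as a marginal (standardised) risk difference with 95% confidence interval, and is performed whatever the baseline comparison shows. An unadjusted Fisher's exact test is a sensitivity analysis.* Delete the opening clause on comparability. The baseline tables can stay as description.

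A random effect for centre is not required: centre is not a minimisation factor, and its effect was not examined here.

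In Number of patients, 862 per arm and 1,896 in total stay unchanged. One added sentence can say that the Fisher-based figure is conservative for the adjusted analysis.

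The cost is a wording amendment. The four covariates are already held by the randomisation system, and no extra patients are needed. Because Trial status reports that recruitment has begun, the change should be dated and made before anyone deciding on it has seen outcomes by arm.

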**Methods/trial design:**

ISAT II is a pragmatic, multicenter, randomized trial comparing clinical outcomes for non-ISAT patients with subarachnoid hemorrhage allocated to coiling or clipping. Inclusion criteria are broad. The primary end-point is the incidence of poor clinical outcome (defined as mRS >2) at one year, just as in ISAT. Secondary end-points include measures of treatment safety for a number of pre-specified subgroups, with efficacy end-points including the presence of a major recurrence at one year; 1,896 patients (862 each arm plus 10% losses) are required to demonstrate a significant difference between coiling and clipping, hypothesizing 23% and 30% poor clinical outcome rates, for coiling and clipping, respectively. The trial should involve at least 50 international centers, and will take approximately 12 years to complete. Analysis will be by intention-to-treat.

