### Study endpoints

The primary end-point, as for the original ISAT study, will be the number of patients experiencing a poor clinical outcome (mRS >2) at one year post-treatment. Secondary end-points include overall mortality at one year (all causes), overall morbidity at one year (all causes), occurrence of a major (saccular) aneurysm recurrence at one year post-treatment, peri-treatment hospitalization lasting more than 15 days, discharge to a location other than home, occurrence of an intracranial hemorrhage after enrollment and for up to one year, occurrence of aneurysm re-rupture following randomization but before treatment initiation, and occurrence of failure of aneurysm occlusion using the intended treatment modality.

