### Stratification of results

Clinical outcomes will be stratified according to the minimization criteria. The Data and Safety Monitoring Board (DSMB) will regularly verify that subgroup treatment outcomes are within the confidence intervals of the study hypotheses.

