### A single large trial or multiple small trials

One of the difficulties specific to our field is the relatively small number, and heterogeneity of patients with rup-tured intracranial aneurysms, which renders well-powered randomized studies addressing specific questions difficult to complete. To mitigate this difficulty, in the spirit of the original ISAT study, we have chosen to keep inclusion criteria broad. This choice of study design has two implications: the first is that at best, a general answer to the question will be obtained, which can, at some future time, be refined by other studies with more narrow inclusion criteria. Although the overall number of patients for whom the uncertainty persists is quite large (perhaps in the range of 40% or more), the reasons why these patients are not typical original ISAT cases are multiple and various. For some clinicians, each individual reason (ie: giant aneurysms, very small aneurysms) could be considered as distinct research questions, and that ISAT-II combines heterogeneous groups that they judge should not be lumped into an overall outcome result, for fear of averaging results that would normally pull in opposite directions. There may be no universally acceptable answer to this problem. Others may fear that by the sheer force of the law of large numbers differences in study population may not be clearly highlighted in demographic statistics or results and we may end up simply ‘repeating ISAT’. Except for depriving patients from a treatment that would have already been shown superior in a previous trial, a possibility that is explicitly excluded in the objectives and hypotheses of ISAT II, what this concern amounts to in actual practice remains unclear. We must, however, remember the first goal of care trials: to protect present patients from unjustified beliefs and hypotheses, and offer optimal care in the presence of uncertainty [[name], [name], Altman DG: Introducing care trials. J Clin Epidemiol 2012. Provisional acceptance]. From an organizational perspective, it is easier to propose a single inclusive large trial than to multiply small trials with narrow selection criteria. It is possible, though, to pre-specify subgroups that will separately be monitored by the DSMB. Thus, the second implication of the ISAT II design choice is that the DSMB must regularly be provided with subgroup-specific safety data to ensure that an emerging obvious discrepancy in clinical outcome will be addressed in a timely manner in order to prevent additional patient morbidity. A randomized context is the only way to firmly establish that one particular treatment modality ought not to continue to be offered to a particular subgroup of patients.

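### One blanket 0.05 rule covers all eight secondary end-points with no order, correction or supportive label, so a false secondary finding has a chance of about 16% to 34% if none truly differs

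*Protocol article*

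**What the plan says.** The Study endpoints section sets one primary end-point, poor outcome (mRS >2) at one year. It then lists eight secondary end-points:

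1. death at one year
2. morbidity at one year
3. major recurrence at one year
4. hospital stay over 15 days
5. discharge elsewhere than home
6. intracranial hemorrhage up to one year
7. re-rupture between randomization and treatment
8. failure to occlude the aneurysm with the intended modality

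Under Number of patients, the primary comparison is planned as a "two-sided Fisher’s exact test" at alpha 0.05 with 90% power, "using estimated 23% and 30% poor clinical outcome rates for endovascular treatment (EVT) and surgical management at one year, respectively".

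Planned analyses repeats the Fisher's exact test for the primary outcome. It assigns t-tests or chi-squared tests to the secondary outcomes and adds regression models that control for baseline data. It ends with "All tests will be interpreted with a 0.05 level of confidence".

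On subgroups, Stratification of results says "Clinical outcomes will be stratified according to the minimization criteria" and gives the DSMB the task of checking subgroup outcomes. It names no test and no significance level for the strata.

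**The concern.** The closing sentence of Planned analyses is a rule, and applying it has a calculable consequence. Each secondary comparison is to be read at the same threshold as the primary, and nothing in the article says that a significant secondary carries less weight. With eight such comparisons, a chance finding on at least one is much more likely than 5%.

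This matters here because the end-points may favour different arms. The primary hypothesis expects fewer poor outcomes with endovascular management. The Background and the Discussion section on patient age report the view that clipping protects better against recurrence. A chance result on one secondary could therefore be cited for either treatment at the nominal level used for the primary, in a trial meant to guide which treatment patients are offered.

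**Working it through.** **Step 1: the primary test is sound.** Inputs from Number of patients: 23% versus 30%, two-sided alpha 0.05, power 90%. Allocation is 1:1 (Method of allocation). The mean rate is 0.265.

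- Without continuity correction: n = [1.960·√(2·0.265·0.735) + 1.282·√(0.23·0.77 + 0.30·0.70)]² / 0.07² = (1.223 + 0.797)² / 0.0049 ≈ 833.3, so 834 per group.
- With continuity correction: n' = (833.3/4)·[1 + √(1 + 4/(833.3·0.07))]² ≈ 861.6, so 862 per group. This is the article's figure.
- Exact power of the two-sided Fisher test at 862 per group is 90.1%.

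The stated alpha, sidedness and sample size agree with each other. The primary is one test of one end-point and has its own 0.05.

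**Step 2: number of secondary tests.** Study endpoints lists eight. Counting one unadjusted between-arm test for each gives k = 8. The baseline-controlled models could add more results under the same rule; they are not counted here.

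**Step 3: chance of at least one p<0.05 if all eight are null.** Each test is taken to have size exactly 0.05.

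- Independent tests: 1 − 0.95⁸ = 1 − 0.6634 = 33.7%.
- Equal pairwise correlation ρ between the test statistics, with c = 1.960: 1 − ∫ [Φ((c − √ρ·u)/√(1−ρ)) − Φ((−c − √ρ·u)/√(1−ρ))]⁸ φ(u) du.

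| Assumed ρ | Chance of at least one false positive among eight |
|---|---|
| 0 | 33.7% |
| 0.1 | 33.2% |
| 0.3 | 30.0% |
| 0.5 | 25.0% |
| 0.7 | 19.1% |
| 0.8 | 15.8% |

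The article gives no correlation, so every row with ρ above 0 is an assumption. Some positive correlation is plausible among death, morbidity, hemorrhage and discharge destination, so the true value may well lie below 33.7%.

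**Step 4: if some secondaries truly differ.** With two real effects, the six remaining null tests still give 1 − 0.95⁶ = 26.5% under independence.

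**Step 5: strata.** The article specifies no stratum test that could be counted, so no error rate is calculated for the strata.

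**The case against.** The strongest reply is that the primary inference is protected. There is one primary end-point with one test, and Planned analyses calls the primary comparisons the main ones, so primary and secondary are ranked at least in name. Unadjusted testing of labelled secondaries beside a single primary is common. No rule declares the trial successful on any one secondary. A condensed article may also leave order and labels to the complete protocol, which Methods: Trial design says is available elsewhere. Much of this stands, and it limits the point to how secondary results may be claimed. It does not remove the point: the article does not leave the level open but fixes 0.05 for every test, and a later document that ranked or adjusted the secondaries would have to depart from that sentence.

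Two stronger readings are tempting, and the article does not support them.

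- A reader might infer that outcomes within each minimisation stratum are also tested at 0.05, and add those tests to the count. That is only an inference from the blanket sentence, since Stratification of results names no test.
- A reader might infer that the secondaries and subgroups are meant as confirmatory. The abstract does write "with efficacy end-points including the presence of a major recurrence at one year", but within a sentence about secondary end-points. The Discussion holds that only randomization can "firmly establish that one particular treatment modality ought not to continue to be offered to a particular subgroup of patients", but that is an argument for randomized evidence, next to a remark on DSMB safety data, and not an analysis rule. The same section expects a general answer at best, and another Discussion section warns that subgroup analyses can mislead and treats them as a source of hypotheses. That warning comes in discussing the original ISAT's subgroups and does not formally label this trial's own results.

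A further objection concerns the remedy. A Holm or Bonferroni family over all eight would require the smallest p-value to reach 0.05/8 = 0.00625, which lowers sensitivity to harm on death, hemorrhage and re-rupture. It would also fit badly with calling the primary the only confirmatory test. This objection is right, and the fix below avoids such a family.

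**Conclusion.** The point holds for the eight secondary end-points. Followed as written, the rule gives a chance of about 34% of at least one false secondary difference if the tests are independent and all null, falling to about 16% at an assumed common correlation of 0.8. That is roughly three to seven times the nominal 0.05 (15.8/5 = 3.2; 33.7/5 = 6.7). The figures assume one test per end-point, each of size exactly 0.05, and equal correlation where it is not zero. The primary test, its error rate and the sample size are not affected, and no claim is made about strata. The sentence should be changed, because it decides what may be concluded from the secondary results, but it does not threaten the trial's main conclusion.

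**What to change.** Replace the closing sentence of Planned analyses with:

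> The Fisher's exact test of mRS >2 at one year is the only confirmatory test, at two-sided 0.05. The eight secondary end-points are supportive and are reported as effect estimates with unadjusted 95% confidence intervals, without confirmatory significance claims. Results by minimisation factor and other subgroups are exploratory, reported as estimates with confidence intervals.

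If the sponsor wants a confirmatory claim on a named efficacy secondary, such as major recurrence, it should be named in advance and tested at two-sided 0.05 only after a significant primary result. That sequence keeps the error rate over the two tests at 0.05. The safety end-points should stay outside any multiplicity adjustment, so that sensitivity to harm is not reduced.

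The cost is wording only: no extra patients, visits or data, and no change to the primary analysis or sample size. The real downside is that secondary results can no longer be claimed as significant at 0.05 in their own right.
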